## Abstract

**Background:**

Inflammatory bowel disease (IBD) is a chronic condition with an unpredictable disease course. Rates of anxiety and depression among IBD patients in relapse (active disease symptoms) as well as in remission are higher than in the general population. Previous studies suggest that the prolonged effect of pain, anxiety, distress and depression have a detrimental effect on patients’quality of life (QoL). Poor QoL in itself is associated with further symptom relapse. Mindfulness based cognitive therapy (MBCT) is a psychological group intervention that has the potential to improve QoL. When used in other chronic conditions, it demonstrated reduced negative effect from pain and psychological factors at completion of an 8-week MBCT course. The effect of MBCT has never been researched in IBD. The aim of this study is to obtain the information required to design a full scale randomised controlled trial (RCT) that will examine the effectiveness of MBCT in improving quality of life for IBD patients.

**Methods/Design:**

This is an exploratory RCT with embedded process evaluation. Forty IBD patients will be recruited from NHS outpatient gastroenterology clinics and will be randomised to either a MBCT (intervention) group or to a wait-list (control) group. All participants will undergo 16 h of structured group training over an 8-week period, with the control group starting 6 months later than the intervention group. Primary outcomes are recruitment, completion/retention rates and adherence and adaptation to the MBCT manual for IBD patients. The secondary outcome is to assess the feasibility of collecting reliable and valid data on proposed outcome measures such as quality of life, anxiety, depression, disease activity and mindful awareness. The process evaluation will use a survey and focus groups to assess the acceptability of the intervention and trial procedures for IBD patients.

**Discussion:**

The outcomes of this study will help define the barriers, uptake and perceived benefits of MBCT program for IBD patients. This information will enable the design of a full-scale study assessing the effect of MBCT on quality of life for IBD patients.

**Trial registration:**

Current Controlled Trials: ISRCTN27934462

## Background

Inflammatory bowel disease (IBD) is a group of relapsing chronic gastrointestinal conditions characterised by inflammation of the gut [1,2]. The condition affects the normal function of the gastrointestinal system, resulting in symptoms such as bloody diarrhoea, vomiting, severe pain and malnutrition [3,4]. It affects approximately 250,000 people in the UK and 28 million worldwide with its incidence rising [5,6]. The two main types are Crohn’s disease (CD) and ulcerative colitis (UC). While there is a concern about the increased risk of colorectal cancer in IBD patients [7], the main burden for patients is the relapsing course of the disease and its detrimental impact on psychosocial functioning and quality of life [8].

### Anxiety, depression and quality of life in IBD

Anxiety and depression rates among IBD patients are higher than in the general population even in remission (when symptoms are settled) [9,10]. Previous studies have suggested that the prolonged effect of pain, anxiety, distress and depression have detrimental effects on quality of life (QoL) [11]. Poor QoL is further associated with symptoms relapse and additional clinical difficulties such as tissue inflammation [12,13]. Anxiety, depression and relapse thus links together in a self-perpetuating cycle with pernicious implications for those affected.

### Use of medication for management of anxiety, depression and pain and its limitations

Evidence suggests that the use of antidepressants can have a positive effect on QoL and symptom management for IBD patients by reducing anxiety and depression [14-16]. This is encouraging. However, some patients using antidepressants have reported unpleasant side effects while others have reported that the antidepressants have no effect on their low mood or anxiety [17-19].

The use of painkillers for pain management also has its limitations. There are subgroups of IBD patients who irrespective of using anti-inflammatory and pain medication continue to suffer severe discomfort, again with a knock-on effect and making symptom exacerbation more likely [20].

In addition, poor medication compliance is frequently reported among IBD patients, with up to 40% of patients regularly omitting their prescribed medications [21,22]. Pharmacology is thus very limited. The search for alternative evidence-based approaches is a pressing concern.

### Mindfulness based cognitive therapy

Mindfulness based cognitive therapy (MBCT) is a non-pharmacological psychological group program designed by Segal et al. [23]. The MBCT program is largely based on the mindfulness-based stress reduction (MBSR) program developed by Jon Kabat- Zinn for coping with stress and chronic illness [24]. Both programs involve teaching individuals various stress management, relaxation, self-care and self-help techniques in a systematic way over an 8-week period. In both, the core skill taught is mindfulness, which uses meditation practice to increase attention and awareness [25]. The working definition of mindfulness in the program is: ‘The awareness that emerges through paying attention on purpose, in the present moment, and nonjudgmentally to the unfolding of experience moment by moment’ [26]. The main difference to the MBSR program is that MBCT has combined cognitive therapy exercises with the mindfulness skill. This combination is believed to further enable patients to increase their awareness and facilitate early recognition of any recurring unhelpful thinking patterns often associated with depressive symptoms and anxiety [23]. Hence, the National Institute for Health and Care Excellence guidelines makes a recommendation for the use of MBCT program as a psychological intervention in the ‘clinical management of persistent sub threshold depressive symptoms or mild, moderate or severe depression in adults (including people with a chronic physical health problem)’ [27].

Although the exact mechanism of how mindfulness-based interventions work is not yet fully understood, the evidence so far suggests that at program completion, participants would experience reduced negative effects from pain, distress, anxiety and depressive symptoms. For example, a systematic review and a meta-analysis of the effectiveness of mindfulness-based interventions on anxiety, depression and psychological distress in patients with chronic pain conditions [28] and chronic medical conditions [29] such as fibromyalgia, cardiac and cancer patients, have shown positive effect on anxiety, depression and psychological distress.

An observational study examining the relationship between mindfulness, QoL, depression and anxiety in patients with ulcerative colitis found a positive association between increasing mindfulness and reducing depression and anxiety [30]. However, MBCT and its effect on QoL has never been researched in a RCT with both Crohn’s and ulcerative colitis patients.

Thus, the MBCT program may be the therapy that can provide a relief from the negative effects of a lifelong management of the disease for IBD patients.

### Hypothesis

The hypothesis is that MBCT will improve QoL scores for IBD patients as well as improve anxiety and depressive symptom scores. This hypothesis is based on previous studies using mindfulness based programs in other chronic condition populations. Hence, the proposed pilot study is the first step towards testing the hypothesis in a definitive RCT and gathering the necessary knowledge to close the existing evidence gap regarding the usefulness of MBCT for IBD patients.

### Aims and objectives

The overall aim of this study is to pilot the MBCT program with IBD patients in a RCT and examine the feasibility of running a large RCT testing the above hypothesis.

The specific objectives of the pilot are:

1. To determine the feasibility of conducting a large-scale RCT of group MBCT for improvement of IBD QoL.

2. To adapt the intervention manual devised by Segal et al. [31], outlining how to carry out an MBCT program for IBD patients.

3. To use data arising from differences between MBCT and control arm to inform a power calculation for sample size of a definitive RCT.

4. Estimate trial eligibility, recruitment (percentage of IBD patients who consent to the trial) and completion/retention rates (percentage of participants completing the trial).

5. To embed a process evaluation within the pilot trial to assess the acceptability of the intervention and trial procedures for IBD patients, such as:

a. Acceptability of recruitment, randomisation and consent procedure

b. Acceptability and feasibility of collecting reliable and valid data on primary and secondary outcomes (including follow-up at 6 months)

c. Fidelity of intervention.

d. Acceptability of length of intervention

e. Appropriateness/suitability of the intervention used

f. Barriers to attendance

g. Expectations about intervention

h. Perceived impact on QoL

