## Methods and design

### Design

This exploratory trial is designed in two phases. Phase 1 is a two-arm pilot RCT (MBCT treatment *vs*. wait-list control group) with three assessments (baseline, post treatment and 6 months). Phase 1 will assess eligibility, uptake, drop-out rates and sample size calculation as well as adaptation and adherence to MBCT manual. This design is consistent with similar studies where a non-pharmacological intervention is investigated in IBD population [32-38].

Phase 2 is a process evaluation assessing the feasibility and acceptability of the intervention, primary and secondary outcomes and trial procedures as well as barriers to attendance and perceived benefits to patients. This design is in line with the Medical Research Council (MRC) framework for the development and evaluation of complex interventions to ensure that both the intervention and trial procedures are optimised and can be incorporated into routine clinical practice [39].

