#### Proposed primary outcome

##### Quality of life

All participants will be required to complete the disease specific IBD quality of life (IBDQoL) questionnaire consisting of 32 questions. The questionnaire has four domains, including bowel symptoms, systemic symptoms, emotional factors and social factors. Within the questionnaire, participants will rate their symptom experience over the previous 2 weeks. Low scores indicate more severe disease activity and/or higher emotional and social dysfunction. A relatively good correlation between the IBDQoL and a widely used measure of disease activity, the Crohn’s Disease Activity Index is reported (*r* = -0.67; *P* <0.001) [46,47].

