### Sample size

The nature of this study is a pilot RCT. Thus, a formal sample size calculation was not performed. The determined sample size of *n* = 40 was calculated based on the estimated number of participants expected to complete the 8-week program.

This number was achieved by the following calculation. Recommendation for pilot sample size calculation is 30 [56,57]. Literature suggest that attrition rate of approximately 25% is to be reasonably expected in mindfulness intervention studies [58]. A sample size of 40 with a 25% attrition rate will give an estimated sample of 30 subjects completing the 8-week program.

The approximate number of IBD patients is 600 in NHS Highland and 1,741 at NHS Grampian. With estimated recruitment rates of IBD interventional studies ranging between 10% and 20% (234 to 468 between the two sides), a sample size of 40 is reasonably achievable.

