### Analysis

Audio-recorded focus groups and interviews with practitioners will be transcribed verbatim. Transcripts will be analysed thematically using the framework analysis approach [59] which is a rigorous method that allows themes to be identified (and organised) within the groups or between the groups. Hence, notable differences in experiences and perceptions can be identified.

From quantitative data we will generate the following: estimates of eligibility, recruitment and retention rates, speed of recruitment, and completion rates of study assessment tools (objectives 1 and 4); Descriptive presentations of the proposed primary and secondary outcomes will be made to inform a sample size calculation for a large-scale trial and decisions as to whether their inclusion would be informative in a future trial (objective 3).

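### Objective 3 names the observed MBCT-control difference as input to the definitive trial's power calculation, but 15 to 20 per arm estimates it too imprecisely to give a stable sample size

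*Protocol article*

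**What the plan says.** Under Aims and objectives, objective 3 reads "To use data arising from differences between MBCT and control arm to inform a power calculation for sample size of a definitive RCT". The Design section adds that "Phase 1 will assess eligibility, uptake, drop-out rates and sample size calculation". The Analysis section ties objective 3 to this: "Descriptive presentations of the proposed primary and secondary outcomes will be made to inform a sample size calculation for a large-scale trial". The outcome proposed for the definitive trial is the "IBD quality of life (IBDQoL) questionnaire consisting of 32 questions".

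On the pilot's own size, the Sample size section says "Thus, a formal sample size calculation was not performed". It gives the basis as "Recommendation for pilot sample size calculation is 30" and "Literature suggest that attrition rate of approximately 25% is to be reasonably expected in mindfulness intervention studies", and concludes "A sample size of 40 with a 25% attrition rate will give an estimated sample of 30 subjects completing the 8-week program". The Randomisation section sets 1:1 allocation.

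The article names no source for the definitive trial's effect size other than the arm differences in objective 3.

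**The concern.** The study exists to supply what is needed to design a full-scale trial, and the sample size is a central part of that. Objective 3 points to the between-arm difference as the quantity that feeds it. Required sample size varies with the inverse square of the assumed difference, so sampling error in the difference is strongly magnified in the resulting N. A pilot that was not sized to estimate a difference can therefore give almost any N. The definitive trial could be planned far too small or needlessly large, with nothing in the calculation to show which.

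**Working it through.** **1. The plan's own figure.** 30 / (1 − 0.25) = 40, which reproduces the stated pilot size. At 1:1 this is 20 randomised and about 15 completing per arm. The 15 is derived, not stated. The 25% refers to completing the course, and outcome data may be more complete than that, so I use 15 to 20 per arm.

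**2. Precision of the difference.** In SD units, SE = √(2/n), and the 95% half-width is t × SE on 2n − 2 df.
- n = 15: SE = √(2/15) = 0.365; 2.048 × 0.365 = 0.75 SD.
- n = 20: SE = √(2/20) = 0.316; 2.024 × 0.316 = 0.64 SD.

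For example, an observed effect of 0.5 SD at 15 per arm has an approximate interval of 0.5 ± 1.96 × √(2/15 + 0.5²/60) = −0.23 to 1.23.

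**3. Effect on the planned N.** Assumptions, none stated in the article: two-sided 5%, 80% power, true effects of 0.3 to 0.8 SD. Required n per arm = 2 × (1.960 + 0.842)² / d² = 15.70 / d². For d = 0.4 this is 98.1, so 99. I simulated pilots, put each observed standardised difference into this formula, and computed the true power of the resulting trial. The last three columns cover only pilots favouring MBCT, since otherwise no meaningful N results.

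| Pilot n per arm | True d | Needed per arm | Wrong sign | Middle half of derived n per arm | Power under 80% | Power under 50% |
|---|---|---|---|---|---|---|
| 15 | 0.3 | 175 | 21% | 41–345 | 63% | 46% |
| 15 | 0.4 | 99 | 14% | 32–227 | 58% | 38% |
| 15 | 0.5 | 63 | 9% | 26–150 | 55% | 32% |
| 15 | 0.8 | 25 | 1% | 14–50 | 51% | 20% |
| 20 | 0.4 | 99 | 10% | 38–233 | 56% | 34% |
| 20 | 0.5 | 63 | 6% | 29–146 | 53% | 28% |

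Derived sizes are rounded up; the quartiles carry small simulation error. Over all pilots, wrong-sign ones included, the observed effect exceeds the true one in 50 to 51%.

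**4. Baseline adjustment.** With an assumed baseline correlation of 0.6, the residual SD is √(1 − 0.36) = 0.8 of the raw SD. The half-width falls to about 0.60 SD at 15 per arm and 0.51 SD at 20. A true 0.4 SD becomes 0.4 / 0.8 = 0.5 residual SD, so the d = 0.5 rows apply: at 15 per arm, 63 needed against a middle half of 26 to 150.

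**5. Planning from the SD only.** With a prespecified target and the pilot's pooled SD on 28 df, planned N is proportional to a chi-square variable divided by 28. Its 10th and 90th percentiles are 0.68 and 1.35 times the correct N. For a target of 0.4 SD that is about 67 to 133 per arm. The same percentiles of difference-based planning, in favourable pilots at 15 per arm, are about 18 to 1,038. The SD point estimate still gives too small an N in 54% of pilots. A one-sided 80% upper limit for the SD is √(28 / 21.59) = 1.139 times the estimate, so N is multiplied by 1.30.

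**The case against.** The strongest reply is that the text is milder than a plan to power the trial on the pilot effect. It says the differences will inform a calculation. The Analysis section promises only descriptive presentations, which would include SDs and completeness. The Data collection section also links attrition from the attendance log to aim 3, so the authors may mean something wider (or this may be a numbering slip). That stands: the article nowhere commits to using the observed difference as the design effect. But objective 3 names that difference and no other source of effect, so if SD-only use was intended, the wording needs the same correction.

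Other limits also stand.
- **Number per arm.** 15 is the low end. Controls have no course to drop out of before 6 months, and non-completers may still return questionnaires. At 20 per arm, or with baseline adjustment, the spread narrows but remains wide.
- **Direction of error.** A reader might infer that the derived trial would usually be too small. That holds only among pilots favouring MBCT, and there the excess is slight at large effects (51% at 0.8 SD). SD-only planning at the point estimate has a similar mild tilt (54%). The spread of N is the argument, not its direction.
- **Wrongly abandoning the trial.** A reader might infer that a chance unfavourable difference would stop the programme. Nothing in the article ties progression to the observed effect; the pilot's primary outcomes concern recruitment, retention, adherence and adaptation of the manual.
- **No minimal important difference named.** This is a condensed article, and the full protocol or analysis plan may give one. The point rests on what objective 3 states, not on that absence.

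**Conclusion.** The concern holds in this limited form: objective 3 directs attention to a quantity that the pilot can estimate only to within about ±0.64 to ±0.75 SD before baseline adjustment. At an assumed true effect of 0.4 SD, the middle half of derived sizes spans roughly a sevenfold range at 15 per arm (227 / 32 = 7.1) and sixfold at 20 (233 / 38 = 6.1). The interval half-widths do not depend on the definitive trial's alpha, power or effect. The figures for derived N and power do, and those inputs are assumptions. The unadjusted calculation ignores clustering by MBCT group, which would widen the interval.

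Severity is should-fix. The pilot's conduct and primary feasibility outcomes are unaffected, and harm arises only if a later design takes the point estimate at face value.

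**What to change.** Reword objective 3 and the linked Analysis sentence to say that:
- the target difference for the definitive trial is a minimal important difference on the IBDQoL, fixed before pilot outcomes are seen;
- the pilot supplies the pooled SD with allowance for its uncertainty (for example an upper confidence limit), the baseline-to-follow-up correlation, and outcome loss by arm;
- the between-arm difference is reported with its 95% confidence interval, and its point estimate is not used as the design effect.

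The cost is wording only, with no new data. The minimal important difference must come from outside this article. An upper SD limit makes the planned N larger than SD-only planning at the point estimate: about 30% with a one-sided 80% limit on 28 df, partly offset by baseline adjustment. That limit is one convention among several, and the 30% is not an increase over any N in the plan, which fixes none for the definitive trial.

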## Methods and design

### Design

This exploratory trial is designed in two phases. Phase 1 is a two-arm pilot RCT (MBCT treatment *vs*. wait-list control group) with three assessments (baseline, post treatment and 6 months). Phase 1 will assess eligibility, uptake, drop-out rates and sample size calculation as well as adaptation and adherence to MBCT manual. This design is consistent with similar studies where a non-pharmacological intervention is investigated in IBD population [32-38].

Phase 2 is a process evaluation assessing the feasibility and acceptability of the intervention, primary and secondary outcomes and trial procedures as well as barriers to attendance and perceived benefits to patients. This design is in line with the Medical Research Council (MRC) framework for the development and evaluation of complex interventions to ensure that both the intervention and trial procedures are optimised and can be incorporated into routine clinical practice [39].

### Setting and recruitment

The study will take place across two health board areas in the north of Scotland, an area comprising of approximately 800,000 people living across a large geographical area including urban and remote rural locations. Recruitment will focus on gastroenterology outpatient clinics.

### Phase 1 - Pilot RCT

#### Participant selection

Less than one-third of RCTs recruit to proposed number [40]. Assessing recruitment is a key component of this study. Ensuring an effective recruitment strategy is thus important. Accordingly, the recruitment strategy devised in this study draws on best evidence [41] tailored to the specific requirements of people with IBD. Specific aspects of the recruitment strategy were developed in collaboration with all parties involved in the care of IBD patients, namely specialist IBD nurse, gastroenterology clinicians and research nurses.

Clinical staff at participating gastroenterology outpatient clinics will identify people who meet the study’s inclusion criteria. They will approach consecutive patients in clinics or by sending an invitation letter with study information and research team contact details. Interested participants will then contact the researcher by telephone or email to register interest. A screening visit with the researcher will then be arranged. Informed written consent will be obtained at the first visit by a member of the research team.

#### Inclusion criteria

1. Be able to verbally communicate and write in English (English does not have to be their first language).

2. Able to give informed consent.

3. Age of 18 years or over (no upper limit).

4. Confirmed diagnosis of Crohn’s disease or ulcerative colitis (by clinician).

5. Ability to do light exercise (for example, to lift arms above the head or bend knees) because part of the practices in the program require this movement.

6. Able to commit to attend the eight sessions (participants should consider their personal circumstances to assess if this is practical and feasible for them).

7. To be able to commit to do home practice of up to 45 minutes daily over the 8 weeks of the study (this is a core component of the program).

8. No change of antidepressants (dose or type) within the last 3 months. Any change of antidepressants within the last 3 months might interfere with the program.

9. Participants will have to be in remission of symptoms.

